### Setting and participants

Participants will be recruited from an existing Internet panel in the Netherlands that is managed by Flycatcher, an ISO-certified institute for online research associated with Maastricht University. Currently, the panel consists of approximately 14,000 active members between 12 and 96 years of age http://www.flycatcher.eu. Members of the panel are recruited online, by written invitation, face to face contacts or by intermediaries. All individuals aged 12 years or older and who have an email address can apply for the panel. Compared with the Dutch population, the panellists are younger, have a higher level of education and are more often female. The total panel is representative of the Dutch Internet population. Panel members receive invitations to participate in online questionnaires approximately eight times per year, and receive an incentive when they have completed a certain number of questionnaires. Variables of the panel members such as age, sex and level of education are provided by Flycatcher.

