### Methods of data collection

An overview of all questionnaires and measures is provided in Table 2 and Figure 1.

**Table 2 T2:** Outcome measures and timing of data collection

Construct	Measures	No. of items	Questionnaire*
*Primary outcomes*			
Knowledge	Knowledge questionnaire based on information provided in the decision aid	20 Statements (True/false/don't know)	2
*Secondary outcomes*			
Attitude	Marteau [26]	4	1,2
Ambivalence	Felt ambivalence [24]	3	1,2
Follow-up behaviour	Uptake of self-tests, visiting a doctor, changing lifestyle.	7	3
Intention	Intention towards self-testing, seeing a doctor.	2	1,2,3
	Intention towards changing lifestyle	1	2,3
	Stages of change [27]	1	1,2,3
Psychosocial determinants	Perceived benefits and barriers	14	2
	Self-efficacy	3	2
	Response-efficacy	4	2
	Perceived susceptibility/risk perception [28]	3	1,2,3
	Cues to action	1	2
	Perceived severity	1	2
	Anticipated regret	1	2
	Moral obligation	2	2
	Subjective norm	1	2

*Questionnaire 1: baseline. Questionnaire 2: directly after seeing intervention or control condition. Questionnaire 3: three months after viewing intervention or control condition

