### Sample size

According to a Cochrane review by O'Connor et al. on the efficacy of decision aids, there is an average absolute increase of 15% in knowledge scores when decision aids are compared to usual care. When more detailed decision aids are compared to simpler decision aids, knowledge increases with 5% [11]. Since we will compare our decision aid to general, non test specific information on self-testing, we expect an increase in knowledge of 15% (intervention group knowledge score 70%, control group 55%). Our sample size will be based on a power of 80% to detect a hypothesized increase in knowledge of 15% at a significance level of 5% (two-sided). Power analysis showed 175 respondents would be needed in each of the four groups [30]. Based on previous research, a completion rate of 60% on the first questionnaire, and 80% on the second questionnaire is expected [3]. Intention towards doing a cholesterol and/or a diabetes self-test in 2008 was 42%. Based on these results, a minimum of 3472 respondents would have to be invited for the first questionnaire. Since we do not know intention rate in 2011, and an unknown number of participants will be excluded because of having cardiovascular disease or diabetes, we decided to invite 6000 panel members for the first questionnaire.

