### Statistical analysis

Knowledge will be treated as primary outcome measure, whereas intention, attitude, ambivalence and psychosocial variables are the secondary outcome measures. To compare knowledge levels and level of ambivalence between the intervention and control group, we will use linear regression analysis. The effect of the decision aid on the psychosocial factors that predict self-test use will be assessed using logistic regression analysis. Follow-up behaviour after 3 months will be compared using logistic regression analysis.

Based on the method proposed by Marteau and colleagues, informed choice will be measured by combining the constructs knowledge, attitudes and behaviour into a composite measure of informed decision making [26]. Informed choice in our study will be defined as having sufficient knowledge, and attitude being in line with intention (positive attitude and a positive intention to do a self-test, or a negative attitude and a negative intention to self-test). As a cut off point for having sufficient knowledge, a score of 50% (number of correct answered questions 10 or above) will be considered. Individual scores will be corrected for guessing using Abbotts' formula [31,32]. A positive intention towards self-testing is defined as a participant indicating to maybe, probably or definitely consider performing a self-test in the future. To classify participants as having a positive or negative attitude towards self-testing, the median score will be used. The median score of the participants and scores above will indicate a positive attitude, whereas scores below the median score will be considered as a negative attitude [26]. The percentage of people with an informed choice in the control and intervention group will be compared using logistic regression analysis.

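### The ambivalence regression gives no role to the scheduled baseline score or to the test group; adding both would gain precision from data already collected

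*Protocol article*

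**What the plan says.** All references are to the protocol article.

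- **Timing.** In Methods of data collection, the Table 2 row that begins "Felt ambivalence [24" is a three-item scale scheduled at Questionnaires 1 and 2. The table footnote makes Questionnaire 1 the baseline and places Questionnaire 2 straight after exposure.
- **Allocation.** Under Randomisation, each participant is first placed in a cholesterol or a diabetes group and is then randomised to decision aid or control within that group.
- **Analysis.** Under Statistical analysis, for knowledge and the "level of ambivalence between the intervention and control group, we will use linear regression analysis". No covariates are listed and none are ruled out. The section does not say whether the two test groups are pooled or analysed separately.
- **Knowledge.** It is measured at Questionnaire 2 only. The Knowledge section says the items are specific to the test, so the two groups answer different quizzes.
- **Size.** Under Sample size, "Power analysis showed 175 respondents would be needed in each of the four groups". That figure is derived for knowledge; no power is given for ambivalence.

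**The concern.** A baseline measurement of the same scale is usually the strongest available predictor of the follow-up score. If it stays out of the model, the variation it explains stays in the residual, the confidence interval is wider than it needs to be, and chance baseline imbalance is not removed from the estimate. This matters for ambivalence because the trial was not sized for it.

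The plan also leaves several analyses open. A comparison of Questionnaire 2 scores, a comparison of changes and a baseline-adjusted comparison all fit the words linear regression. They differ in precision and, under chance imbalance, in the estimate. Research question 3 asks about a difference in level, while the Discussion expects ambivalence to decrease, so the text does not settle which is meant.

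The test group raises a similar issue. If the groups are pooled, any difference between them in mean ambivalence, or in mean score on two different knowledge quizzes, goes into the residual unless the model has a term for it.

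**Working it through.** **1. The plan's own figures.** Inputs from Sample size: knowledge 70% against 55%, power 80%, and testing "at a significance level of 5% (two-sided".

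- Two proportions: 163 per group without continuity correction, 176 with it.
- Two means with a difference of 0.15 and an SD of 0.5: n = 2 × (1.960 + 0.842)² × 0.5² / 0.15² = 174.4, so 175.
- Invitations: the plan assumes "a completion rate of 60% on the first questionnaire, and 80% on the second questionnaire is expected", and an intention rate of 42%. 4 × 175 / (0.60 × 0.80 × 0.42) = 3472.2, against the stated 3472.

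The stated size is reproduced. It concerns knowledge, which has no baseline measure, so nothing below changes it.

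**2. Gain for ambivalence.** Let r be the within-arm correlation between the Questionnaire 1 and Questionnaire 2 scores. The documents give no value, so r is assumed over 0.3 to 0.8. For a linear model with a common slope and equal variances in the arms:

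- variance of the adjusted difference = (1 − r²) × variance of the unadjusted difference
- detectable standardised difference, unadjusted = (1.960 + 0.842) × √(2/n)
- detectable standardised difference, adjusted = the unadjusted value × √(1 − r²)
- power at the unadjusted detectable difference = Φ(2.802/√(1 − r²) − 1.960)
- equivalent unadjusted n per arm = 175/(1 − r²)

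Unadjusted values: 2.802 × √(2/175) = 0.300 within one test group, and 2.802 × √(2/350) = 0.212 with both groups pooled.

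| Assumed r | Variance cut (r²) | Detectable, 175 per arm | Detectable, 350 per arm | Power where unadjusted has 80% | Equivalent n for 175 |
|---|---|---|---|---|---|
| none (unadjusted) | 0% | 0.300 | 0.212 | 80% | 175 |
| 0.3 | 9% | 0.286 | 0.202 | 84% | 192 |
| 0.5 | 25% | 0.259 | 0.183 | 90% | 233 |
| 0.7 | 49% | 0.214 | 0.151 | 97.5% | 343 |
| 0.8 | 64% | 0.180 | 0.127 | over 99% | 486 |

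Differences are in units of the unadjusted SD of the ambivalence score.

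**3. Availability of the covariate.** Questionnaire 1 is the selection questionnaire and comes before randomisation. If it carries the ambivalence items, everyone randomised should have a baseline score, apart from skipped items.

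**4. Test-group term.** The documents give no expected difference in ambivalence or knowledge between the cholesterol and diabetes groups, so this gain cannot be sized. The reasons for the term are the allocation within test group and, for knowledge, the two different quizzes.

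**The case against.** The strongest objection is that the article is silent on covariates and states no unadjusted analysis. Linear regression is the very model that baseline adjustment uses, scheduling ambivalence at baseline is consistent with it, and a condensed article often leaves the covariate list to a fuller document. This stands to the extent that a reader might infer a comparison of post-exposure scores only, with the baseline thrown away; the text does not say so. It does not remove the point. The same section fixes the knowledge cut-off, the guessing correction and how scores at the attitude median are classified, yet gives the baseline ambivalence score no use.

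A reader might also extend the argument to attitude, intention and risk perception, which Table 2 also lists at baseline. The plan does not support that:

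- Attitude and intention have no stand-alone comparison between arms. They enter the informed-choice composite as dichotomies, analysed by logistic regression.
- Eligibility admits only people answering maybe, probably or definitely, all of which the analysis section counts as positive, so dichotomised baseline intention cannot vary.
- Risk perception is listed among the psychosocial determinants, for which logistic regression is stated. There, adjustment turns the odds ratio into a conditional one and does not shrink its standard error, so the 1 − r² figure does not carry over.

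For knowledge, one might propose age, sex and education as covariates, since "Variables of the panel members such as age, sex and level of education are provided by Flycatcher". That is reasonable, but nothing in the documents sizes the gain, and leaving them out is no error in a randomised comparison.

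Finally, an unadjusted comparison is unbiased under randomisation and its confidence interval already allows for chance imbalance. That is correct and limits the point to precision.

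**Conclusion.** The point holds as a modest precision gain on one secondary outcome. For an assumed correlation of 0.3 to 0.8, adjusting ambivalence for its own baseline reduces the variance of the between-arm difference by 9% to 64%, and the detectable difference with 175 per arm drops from 0.300 to 0.286–0.180. At the low end of that range the gain is small.

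This rests on the assumed correlation, on a linear relation that is similar in both arms, and on Table 2 being right that ambivalence is collected at Questionnaire 1. The prose description of that questionnaire mentions personal characteristics and intention but not ambivalence, so the two should be reconciled.

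No bias is claimed, and neither the 175 per group nor the number invited is affected. The test-group term is justified by the design, but its gain is unquantified.

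**What to change.** Add to Statistical analysis, before the data are analysed: Questionnaire 2 ambivalence will be analysed by linear regression on arm and Questionnaire 1 ambivalence, with a term for test group (cholesterol or diabetes) if the two groups are pooled; a pooled knowledge regression will include the same test-group term. State whether the groups are pooled, and confirm in the description of Questionnaire 1 that the ambivalence items are included.

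The cost is a sentence or two of text. On Table 2's schedule it needs no new data, no extra respondents and no added burden, and the model spends one degree of freedom per added term.

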### Study aim and research questions

The principal aim of the proposed study is to evaluate the effect of the decision aid on knowledge of on self-testing. The following research questions were formulated:

1. Do consumers who have been exposed to the decision aid have more knowledge of self-testing than the control group?

2. Do consumers who have been exposed to the decision aid more often make an informed choice in self-testing than consumers in the control group?

3. Do the intervention and control groups differ in level of attitudinal ambivalence?

4. What is the effect of the decision aid on the psychosocial factors that predict self-test use for diabetes and cholesterol?

5. Is there a difference between the intervention and control group in follow-up behaviour 3 months after the use of the decision aid?

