##### Ambivalence

Felt ambivalence will be assessed using a 3 item scale as described by Priester and Petty [24].

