##### Psychosocial determinants

Possible determinants of self-test use were derived from the Health Belief Model (HBM) [16], as well as several concepts of the Theory of Planned Behavior (TPB) [17] and will be assessed after participants have viewed the decision aid or control condition.

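### Research question 4 is given logistic regression, although most of its outcome items belong to multi-item psychosocial constructs for which no cut-off is defined

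*Protocol article*

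**What the plan says.** Research question 4, under Study aim and research questions, asks: "What is the effect of the decision aid on the psychosocial factors that predict self-test use for diabetes and cholesterol". The Statistical analysis section confirms that these variables are outcomes: "intention, attitude, ambivalence and psychosocial variables are the secondary outcome measures". For this question it then names the model: "The effect of the decision aid on the psychosocial factors that predict self-test use will be assessed using logistic regression analysis".

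Table 2 (Methods of data collection) lists nine psychosocial constructs with their item counts. The largest is "Perceived benefits and barriers", with 14 items. The Psychosocial determinants section says that the determinants "will be assessed after participants have viewed the decision aid or control condition". Table 2 adds that perceived susceptibility/risk perception is also collected in Questionnaires 1 and 3.

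The nearest comparable outcome is handled differently. On ambivalence the article says: "Felt ambivalence will be assessed using a 3 item scale". Its model is linear: "To compare knowledge levels and level of ambivalence between the intervention and control group, we will use linear regression analysis".

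**The concern.** The decision aid is the exposure and the psychosocial factors are the outcomes. In its usual binary form, logistic regression needs an outcome with two categories. A construct measured by 3, 4 or 14 items will normally give a score with many values, so it must be cut in two before that model can be used. The article states no cut. Choosing cuts after the data are seen leaves room for selective results on each construct, and cutting a score loses power.

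The closing words of the sentence, on factors that predict self-test use, also allow a different reading: a logistic model with self-test use as the dependent variable and the factors as predictors. That would answer a question about prediction. It would not answer research question 4.

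**Working it through.** **1. What kind of outcomes these are.** Item counts from Table 2:

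| Construct | Items |
|---|---|
| Benefits and barriers | 14 |
| Response-efficacy | 4 |
| Self-efficacy | 3 |
| Susceptibility/risk perception | 3 |
| Moral obligation | 2 |
| Cues to action | 1 |
| Severity | 1 |
| Anticipated regret | 1 |
| Subjective norm | 1 |

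Multi-item constructs: 5 of 9. Items in them: 14 + 4 + 3 + 3 + 2 = 26, of 26 + 4 = 30 in all. The majority is narrow by construct and clear by item.

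**2. Which cut-offs the article defines.** There are three, all serving the informed-choice measure: knowledge at 50%, intention at maybe or higher, and attitude by the median ("To classify participants as having a positive or negative attitude towards self-testing, the median score will be used"). None applies to a psychosocial construct.

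**3. Side by side.** Felt ambivalence has 3 items and gets linear regression. Self-efficacy has 3 items and gets logistic regression in the next sentence. No reason is given for the difference.

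**4. The plan's sample size, as the base for an illustration.** Inputs from the Sample size section: 55% against 70%, two-sided 5%, power 80%. The two-proportion formula gives 163 per group without continuity correction and 176 with it, so the stated 175 in each of four groups is reproduced. The invitation figure also follows: 4 × 175 / 0.80 / 0.60 / 0.42 = 3472. Nothing is wrong here.

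**5. What a median split would cost (illustration).** The article gives no SD or distribution for these measures. Assume a normal score with equal SD in both arms.

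- Efficiency of a median split relative to the comparison of means, for small effects: 2/π = 0.637, about 64%.
- Difference detectable with 80% power by linear regression at 175 per group: d = (1.960 + 0.842) × √(2/175) = 0.30 SD.
- After a split midway between the arms, the proportions above the cut are Φ(−0.15) = 0.440 and Φ(0.15) = 0.560.
- Power = Φ{[0.119 × √175 − 1.960 × √(2 × 0.5 × 0.5)] / √(0.440 × 0.560 + 0.560 × 0.440)} = Φ{(1.575 − 1.386) / 0.702} = Φ(0.269) = 0.606.
- With the cut at the control-group median instead (0.500 against 0.618), power is 0.602.
- Restoring 80% would take 276 to 279 per group, about 1.6 times 175.

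If the two test groups are pooled to 350 per arm, the detectable difference is 0.21 SD, power after the split is 0.61, and 551 per arm would be needed. The proportional loss is the same.

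Uneven cuts cost more. At 175 per group and the same 0.30 SD, power is 53% to 58% if 70% of controls lie above the cut, and 32% to 41% if 90% do, depending on the direction of the effect.

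**6. The alternative reading.** Follow-up behaviour is research question 5 and has its own logistic regression sentence directly afterwards. A model of self-test use on the factors would have the factors on the right-hand side, so it cannot yield the effect of the decision aid on them. Because the factors are measured after exposure, an arm coefficient in such a model would not be the total randomised effect either.

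**The case against.** The strongest reply is that the article never says how the items are scored. Item counts do not prove sum scores. The questionnaires are in additional files that are not shown, and some items, such as cues to action, could be binary. Scoring rules are also the kind of detail that an article leaves to a fuller document. This stands as a limit on certainty. It does not remove the point, because the model is stated rather than left open, and ambivalence shows that the article treats a 3-item scale as continuous.

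A reader might infer that the sentence can be carried out only by dichotomising or by modelling self-test use. The documents do not support that. Ordinal logistic regression is a member of the same family and could suit the single ordered items. A logistic model with arm as the dependent variable and a score as predictor would need no cut; its univariable score test is asymptotically equivalent to comparing means. The article mentions neither, and the second would not express the effect of the aid in units of the score.

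A reader might also infer that the article plans self-test use as the outcome for this question. It does not say so. The phrase repeats the wording of research question 4, where it describes the factors. It is one possible reading only.

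Finally, a reader might take 64%, or 350 × 0.637 = 223 effective participants per arm, as the actual cost of the plan. That would need a normal score, a median split and pooled test groups. The article specifies none of these for the psychosocial measures.

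**Conclusion.** The point holds in a limited form. The article fixes a model that fits multi-item scores badly, gives no cut-points that would make binary logistic regression workable, and departs without explanation from its own treatment of ambivalence. If scores were split at the median, an 80% power comparison would fall to about 60%, assuming a roughly normal score; other cuts would lose more. These figures show the order of the loss and do not measure what the plan will lose.

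The consequence is confined to a secondary research question. The analyses of knowledge (the primary outcome), ambivalence, informed choice and follow-up behaviour, and the sample size, are not affected. The change is worth making before analysis because as written the reader cannot tell which variable is dependent or how the multi-item constructs enter the model.

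**What to change.** Replace the sentence for research question 4 with a statement along these lines:

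- Each multi-item psychosocial score from Questionnaire 2 is the dependent variable in a linear regression on trial arm and test group (cholesterol or diabetes). For risk perception, the Questionnaire 1 value is added as a covariate.
- Single ordered items are analysed with an ordinal model.
- Binary logistic regression is kept for items that are truly binary.
- Any model of which factors predict self-test use is reported as a separate, exploratory, non-randomised analysis.

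Before finalising, check the response formats in the additional files, list any items that are already binary, and state how each multi-item construct is scored, including whether benefits and barriers form one score or two. The cost is a few lines of text. No new data and no change to the sample size are needed.

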## Discussion

This paper describes the protocol for a randomised controlled trial to evaluate the effect of an online decision aid for self-testing on diabetes and cholesterol. Since self-testing on these conditions can be beneficial but can have negative implications as well, the goal of the decision aid 'zelftestwijzer' was not to increase or decrease uptake of these tests, but to enhance knowledge levels and to guide the decision making process. Self-testing uptake in the past often seemed to be associated with offering of free tests and media campaigns stressing the importance of testing, and consumers responding quite straightforward, being curious about testing and wanting to be reassured on their health status [9]. Although these strategies seemed to increase uptake levels, consumers will often not have considered important pitfalls of self-testing [3]. Also, consumers with an intention towards self-testing experience several barriers to self-testing, especially a lack of knowledge on interpreting the results ([name] et al: An intention to self-testing: a qualitative study regarding consumers' considerations and information needs about self-testing, submitted). For this reason, the primary outcome of this study is knowledge of on self-testing. We expect knowledge levels of participants who have viewed the decision aid to increase. Being aware of the pitfalls of self-testing, but also of the positive effects of self-testing, consumers should be enabled to make a choice regarding self-testing they think is the best choice for them. We expect levels of informed choice to increase, and levels of ambivalence to decrease. We will measure actual uptake of self-tests 3 months after viewing the decision aid, to assess if there are changes in uptake of tests between the intervention and the control group.

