To support consumers in deciding whether they want to perform a self-test or not, objective information on self-tests could be provided to stimulate consumers to weigh the pros and cons of self-testing. Their decision should be based on knowledge as well as personal values, in which these personal values are related to intention, for example, a positive attitude should lead to a positive intention; a so-called informed choice. Consumers with an intention towards self-testing indicated they experienced benefits as well as barriers in self-testing. In other words, they experienced feelings of ambivalence towards self-testing [10]. If these feelings are not resolved and people have to make a decision, they experience feelings of discomfort. Therefore, ambivalent attitude holders have the urge to integrate these feelings into one response; they want to 'choose sides' [10]. To support patients in making a choice that is the best choice in their specific situation, for example for patients facing treatment and screening decisions, decision aids have been developed. These decision aids have shown to improve people's knowledge of options and reduce difficulty in decision making [11].

We developed a web-based decision aid on self-testing http://www.zelftestwijzer.nl, which provides information on self-tests in general, and test specific information on self-tests for diabetes and cholesterol. The web-based decision aid was based on clinical practice guidelines, previous research on self-testing [3,9,12,13], the International Patient Decision Aid Standard (IPDAS) [14,15], and the Health Belief Model (HBM) [16]. The decision aid provides information on self-testing, as well as a value clarification tool to weigh the pros and cons of self-testing. The aim of this study is to investigate the effect of the web-based decision aid on knowledge of self-testing, informed choice, ambivalence and psychosocial concepts.

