#### Ambivalence

In previous research we found that individuals who intend to perform a cholesterol or diabetes self-test perceived strong benefits as well as strong barriers towards using a self-test ([name] et al: An intention to self-testing: a qualitative study regarding consumers' considerations and information needs about self-testing, submitted). Individuals who hold both strong positive and negative beliefs or feelings towards a certain action or attitude object are considered to be ambivalent [10]. An important distinction needs to be addressed concerning the ambivalence concept, namely the difference between potential ambivalence [23] and felt ambivalence [24]. Potential ambivalence concerns the coexistence of beliefs that are associated with incongruent evaluations related to a certain behaviour or attitude object. Individuals do not necessarily have to be aware of this incongruence and therefore potential ambivalence can be implicit. Felt ambivalence refers to simultaneously having positive and negative emotions towards a certain behaviour or attitude object. For felt ambivalence to occur, the individual needs to be aware of his conflicting feelings between the two sides of the behaviour or attitude object. These conflicting feelings lead to psychological discomfort which is experienced as being unpleasant. Ambivalent attitude holders are motivated to solve this psychological discomfort by integrating their conflicting feelings in one evaluate response. When this is achieved, ambivalence and the related psychological discomfort are solved [10,25].

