### Inclusion and exclusion criteria

Panel members aged 18 or older, with an intention to use a diabetes and/or a cholesterol self-test in the future will be invited to participate in the randomised controlled trial. An intention will be defined as a consumer indicating to maybe, probably, or definitely intending to use a self-test in the future. People who report that they are already diagnosed with diabetes and/or a cardiovascular disease will be excluded from this study.

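### The ambivalence comparison makes no stated use of the baseline felt-ambivalence score, although the effect may differ with initial ambivalence and the average may be diluted

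*Protocol article*

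**What the plan says.** All references are to the protocol article.

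- **Question.** Research question 3 (Study aim and research questions) is: "Do the intervention and control groups differ in level of attitudinal ambivalence". It names no direction and no subgroup.
- **Expectation.** The Discussion gives the direction: "We expect levels of informed choice to increase, and levels of ambivalence to decrease".
- **Mechanism.** The theory section on ambivalence explains it: "Ambivalent attitude holders are motivated to solve this psychological discomfort by integrating their conflicting feelings in one evaluate response". The same section separates potential ambivalence, which a person may not notice, from felt ambivalence, which requires noticing the conflict.
- **Entry.** Inclusion and exclusion criteria: "An intention will be defined as a consumer indicating to maybe, probably, or definitely intending to use a self-test in the future". No level of ambivalence is required.
- **Measure.** Under Measures: "Felt ambivalence will be assessed using a 3 item scale". Table 2 lists it at Questionnaire 1 (baseline) and Questionnaire 2 (straight after exposure).
- **Analysis.** Statistical analysis: "To compare knowledge levels and level of ambivalence between the intervention and control group, we will use linear regression analysis". The section does not say what is done with the Questionnaire 1 score.

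**The concern.** The mechanism concerns people who already feel conflict and want to settle it. Entry on intention also admits people who feel little or none, for example those firmly set on testing. For them there is little to resolve, and the aid may even raise ambivalence. The value clarification tool puts six disadvantages beside six advantages, and the Discussion says that consumers have often overlooked the pitfalls. If noticing both sides is what makes ambivalence felt, a one-sided user may leave the aid more torn than before.

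The effect may therefore vary with the starting level. A small average difference would then have two readings: the aid does little for anyone, or it helps those who were ambivalent and the remainder dilute the result. The variable that would help to tell these apart appears in Table 2, but the analysis text gives it no role. A split by baseline chosen after a null result would carry little weight.

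**Working it through.** **1. The plan's own figure.** The Sample size section is for knowledge only: 55% against 70%, two-sided 5%, 80% power.

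n = [1.96·√(2·0.625·0.375) + 0.8416·√(0.55·0.45 + 0.70·0.30)]² / 0.15² = (1.342 + 0.569)² / 0.0225 ≈ 162.3, so 163 per group. With continuity correction it is 176. The stated 175 therefore reproduces, within rounding, with the correction. Invitations: 4·175 / (0.80·0.60·0.42) = 3472, as stated. No effect size or SD is given for ambivalence.

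**2. What these numbers can detect for ambivalence.** The detectable difference in SD units at 80% power is (1.96 + 0.8416)·√(2/n). At 175 per arm (one test) it is 0.30. At 350 per arm (both tests pooled) it is 0.21.

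**3. Dilution, under assumptions.** Let d be the effect in people who start ambivalent and p the share in whom the aid has no effect. The documents give neither. The average effect is (1 − p)·d, and power is Φ[(1 − p)·d / √(2/n) − 1.96], taking SD 1 in all groups.

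| p | Average if d = 0.30 | Power, 175 per arm | Power, 350 per arm |
|---|---|---|---|
| 0 | 0.30 | 80% | 98% |
| 10% | 0.27 | 71% | 95% |
| 25% | 0.225 | 56% | 85% |
| 50% | 0.15 | 29% | 51% |

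The sample needed to restore power grows by 1/(1 − p)²: 1.23, 1.78 and 4 times at 10%, 25% and 50%. With d = 0.50 and p = 25%, power is still 94% at 175 per arm and above 99% at 350.

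**4. An opposite effect.** If ambivalence rises by u in the share p, the average is (1 − p)·d − p·u. It is zero only when p = d/(d + u): 50% if u = d, 67% if u = d/2, 80% if u = d/4. Short of that, with d = 0.30, u = d/2 and p = 25%, the average is 0.225 − 0.0375 = 0.1875, with power 42% at 175 per arm and 70% at 350.

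**5. How well a baseline-by-arm term could be estimated.** For two baseline groups with shares p and 1 − p, the standard error of the difference in effects is √[2/(np) + 2/(n(1 − p))]. With p = 0.5 this is √(8/175) = 0.214 or √(8/350) = 0.151. For a true difference of 0.30 SD, power is Φ(0.30/0.214 − 1.96) = 29% and Φ(0.30/0.151 − 1.96) = 51%.

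**6. The covariate itself.** Adjusting for the baseline score multiplies the residual variance by about 1 − r², where r is the correlation between the two measurements. The documents do not give r, but any non-negligible correlation improves the overall comparison.

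**The case against.** The strongest reply is that the planned comparison fits the stated question. Research question 3 and the Discussion both speak of group levels, and the average difference between randomised arms is a valid answer for the enrolled intenders. This stands. A reader might infer that the expected decrease cannot be judged at all from the planned contrast. That follows only if the hypothesis is rewritten as a claim about people who start ambivalent, which the article does not do.

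Second, entry by intention has a stated reason. The Background says of consumers with an intention: "In other words, they experienced feelings of ambivalence towards self-testing [10". Nothing shows that a material share starts at the bottom of the scale. This stands in part. The support is qualitative, gives no share, and shows advantages and barriers held together. By the article's own distinction, such beliefs can coexist without being felt.

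Third, a person at the scale minimum at baseline cannot fall below it, but could drift upward under control through measurement noise. The aid could then still lower that person's score relative to control. The factor (1 − p) is therefore an assumption about where the effect is absent, not a consequence of the floor. This stands.

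Fourth, an analysis plan that is not shown may already include the covariate or a moderator analysis, and linear regression leaves room for both. This also stands, and it limits the point to what the article fixes.

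**Conclusion.** The point holds in a limited form. The analysis text gives no role to a baseline score that Table 2 collects, while the article's own account of felt ambivalence gives reason to expect an effect that varies with that score. The average comparison remains a valid answer to research question 3, but alone it cannot show where an effect lies.

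The size cannot be determined. For an assumed 0.30 SD effect, the loss is slight if 10% do not respond and both tests are pooled (98% to 95%), and serious if half do not respond (80% to 29% at 175 per arm, 98% to 51% at 350). These figures assume SD 1 throughout, a normal approximation and no effect in the share p.

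Two stronger readings are tempting and unsupported. One is that participants without ambivalence do cancel the effect. Cancellation needs a rise in some participants, which is plausible on the article's theory but not shown, and a large share, 50% if rise and fall are equal. The other is that the hypothesis should be judged only in people above the scale minimum. That would replace the question the article asks.

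The outcome is secondary, so the point does not touch the main result. It relies on Table 2 for the baseline measurement, because the prose description of Questionnaire 1 mentions only personal characteristics and intention.

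**What to change.** In Statistical analysis, state that the model for research question 3 includes the Questionnaire 1 felt-ambivalence score as a covariate, and that the overall adjusted arm contrast is the main answer.

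As a pre-specified secondary estimate, add the product of baseline score and arm. Report the arm effect with its confidence interval at baseline values fixed before the data are seen. Present this as an estimate and not as the test of the hypothesis, because its power is low and a null interaction would not show that the effect is uniform.

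The cost is a sentence or two of analysis wording and one more secondary estimate. Given Table 2, no new data are needed, and entry need not change. If the unseen analysis plan already contains these terms, a line in the protocol pointing to it is enough.
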